### 2.6 Sample size and statistical power

Sample size estimates were based on a non-inferiority design. Considering a one-sided type I error α = 0.025, a type II error *ß* = 0.10, a non-inferiority margin δ = − 8%, a proportion of the successful anesthesia induction and maintenance of 98% in both treatment groups, and an intervention: control ratio of 3: 1. One hundred seventy-one pediatric patients were calculated using PASS Version 15.0 (NCSS, United States). Together with an expected loss to follow-up of 10%, we required a total of 192 pediatric patients (144 in Group R, 48 in Group P). The proportion of the successful anesthesia induction and maintenance of 98% in both treatment groups was set under pre-test in pediatric patients and previous studies in adults (Doi et al., 2020; Sheng et al., 2020; Dai et al., 2021).

### 2.7 Statistical methods

All randomized patients who will receive at least one treatment specified in the trial will be included in the full analysis set (FAS). Continuous variables will be tested for normality using a Shapiro-Wilk normality test. Demographics and all endpoints will be presented as numbers and percentages (dichotomous variables), means and standard deviations (normally distributed continuous variables), and medians and interquartile ranges (non-normally distributed continuous variables). Comparison between groups of all dichotomous endpoints will be analyzed with the χ2 test, continuity correction χ2 test or Fisher’s exact test whenever it is appropriate. We will compare the normally distributed continuous endpoints using independent samples *t*-test and calculate the difference (and 95% CI of the difference) between means. Non-normally distributed continuous endpoints will be compared using Mann–Whitney *U* test, and the difference (and 95% CI of the difference) between medians will be estimated using Hodges–Lehmann estimators. Non-inferiority will be assumed if the lower limit of a two-sided 95% CI of the difference between Group R and Group P in the percentage of participants meeting the primary endpoints exceeds the non-inferiority margin. Missing data will be considered to be missing at random without data imputation. Available case analysis will be implemented to handle missing data such as PHBQ-AS score measured during follow-up. *p*-value < 0.05 will be considered statistically significant. Data analysis will be performed using SPSS version 26.0 for Windows (SPSS Inc., Chicago, IL, United States).

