### 2.3 Randomization and masking

After giving consent, eligible children will be randomized by an interactive web response system (IWRS) at a 3:1 ratio into the remimazolam group (Group R) or propofol group (Group P). Randomization will be stratified by centers to limit baseline imbalance between treatment groups. All study drugs will be prepared by a designated researcher with a stock solution of propofol (10 mg/mL, Fresenius Kabi Austria GmbH, Graz, Austria) and remimazolam tosylate (36mg, Jiangsu Hengrui Pharma Corporation, China) dissolved in sterile saline solution 0.9% to a concentration of 1 mg/mL. In consideration of the obvious difference in drug color and dose adjustments, only the participants will be blinded to the treatments throughout the study. Trained outcome evaluators blinded to group allocation will be assigned to assess the prescribed endpoints after the operation.

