### 2.5 Outcomes

The primary endpoint will be the incidence of the successful induction and maintenance of anesthesia. Successful anesthesia induction will be defined as LoC being reached without the use of remedial sedative drugs during the induction period. Successful anesthesia maintenance will be defined as neither need for rescue sedative medication nor discontinuity of investigational drugs during the maintenance period.

The secondary endpoints will include 1) time to LoC: the time interval from an initial dose of investigational drugs to the first MOAA/S score ≤1; 2) usage of additional sedative drugs during the induction period; 3) the BIS value before dose, at LoC, after tracheal intubation and during the maintenance of anesthesia (LoC to end of the investigational drugs); 4) awakening time: the time interval from the end of investigational drugs to the first of 3 consecutive MOAA/S scores of 5; 5) extubation time: the time interval from discontinuation of investigational drugs to extubation; 6) the incidence of ED, moderate and severe pain (FLACC scale >3) in PACU; 7) usage of remedial drugs in PACU; 8) PACU discharge time: the time interval from the end of investigational drugs to the first of 2 consecutive modified Aldrete score ≥9; 9) parental and anesthesiologists satisfaction; and 10) the incidence of negative behavior change at day 3 after surgery.

Safety endpoints will include frequency, causality, and severity of adverse events (AEs) in each treatment arm. Grading of AEs will be according to Common Terminology for Adverse Event (CTCAE), Version 5.0 criteria. Injection site pain, fluctuations in blood pressure or heart rate, and the use of vasoactive agents will be recorded. Postoperative nausea and vomiting (PONV), delayed awakening from anesthesia, and respiratory depression will also be collected.

Detailed information about surgery will be collected: name of surgery, length of surgery, intraoperative bleed loss, the total maintenance dose of study drugs (remimazolam or propofol) and remifentanil, total cumulative additional consumption, frequency of fentanyl and cis-atracurium, and usage of perioperative concomitant medication.

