
Hence, the striking features of remimazolam include faster onset and offset rates, a shorter half-life than midazolam and dexmedetomidine, lower accumulation and risk of cardiovascular and respiratory depression than propofol, and availability of a reversal agent, which should be sufficient to increase the accuracy of the hypothesis—non-inferior efficacy and more limited AEs of this drug in induction and maintenance of general anesthesia in preschool-age children than propofol. Particularly, it should be suitable for short-term operations and day-surgery where the child needs to be discharged from the hospital as early as possible.

In our research, we will include 192 children aged 3–6 years to explore the efficacy and safety of remimazolam in preschool-age children in consideration of the large variation in physiological changes in children which leads to large differences in pharmacokinetic processes, and the difficulty in establishing peripheral venous access preoperatively in children under 3 years of age. We choose propofol as the control drug instead of midazolam or dexmedetomidine, mainly because propofol is the most commonly used intravenous agent for the induction and maintenance of anesthesia, procedural, and critical care sedation in pediatric patients (Chidambaran et al., 2015). Furthermore, midazolam and dexmedetomidine have always been used as premedications for pediatric patients to relieve anxiety and distress, enhance compliance with anesthesia induction, and reduce the incidence of ED (Lang et al., 2020).

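### Section 2.7 fixes unadjusted two-group tests for every secondary endpoint and ignores center, age and booked operation; this gives up some precision but is not an error.

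*Protocol article*

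**What the plan says.** Section 2.7 (Statistical methods) sets the between-group comparison by type of variable:

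- Binary endpoints: "Comparison between groups of all dichotomous endpoints will be analyzed with the χ2 test", or its continuity-corrected form or Fisher's exact test.
- Continuous endpoints judged normal: "We will compare the normally distributed continuous endpoints using independent samples *t*-test", with a difference in means and its 95% CI.
- Other continuous endpoints: "Non-normally distributed continuous endpoints will be compared using Mann–Whitney *U* test", with a Hodges–Lehmann difference and its 95% CI.

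No regression, stratified or otherwise adjusted analysis appears in the article.

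On allocation, section 2.3 says: "Randomization will be stratified by centers to limit baseline imbalance between treatment groups". There are three centers (section 2.1), and age and operation are not stratification factors. Both are known beforehand. Demographic data are taken at the pre-anesthesia visit (section 2.4.1), and eligibility requires a booked elective operation under intubation, with cardiothoracic, neurosurgical and hepatic surgery excluded (section 2.2.1). Section 2.5 adds: "Detailed information about surgery will be collected: name of surgery, length of surgery". The arms are 144 and 48 (section 2.6), and recruitment is under way (section 2.1).

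**The concern.** The secondary endpoints include recovery times, emergence delirium, pain, remedial drugs in PACU and day-3 behavior. Age and type of operation could plausibly predict several of them. The Discussion calls pain a key confounder of delirium and of behavior change, and the planned operation is a natural pre-treatment proxy for pain. With 48 children on propofol, age and case mix are balanced only by chance, and the planned tests use neither. They also leave out center, although allocation is stratified on it.

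Precision matters here because the Discussion states a second hypothesis: that the two drugs do equally well on delirium and negative behavior. A claim of similarity is only as good as the width of its interval.

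**Working it through.** **The plan's own figure.** With 98% success in both arms, margin 0.08, one-sided α 0.025, power 90%, ratio 3:1 and unpooled variance:

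- Controls = 0.98 × 0.02 × (1 + 1/3) × (1.960 + 1.282)² / 0.08² = 42.9, or 171.6 in total. The article gives 171 (128 + 43).
- 171 / 0.90 = 190, which rounds up to 192 in multiples of four.

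The sample size reproduces and is not at issue. It concerns the primary endpoint only.

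**Chance imbalance at 144 v 48.**

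- SE of a mean difference in SD units = √(1/144 + 1/48) = 0.167. The 95% range is ±1.96 × 0.167 = ±0.33 SD.
- P(age imbalance above 0.25 SD) = P(|Z| > 0.25/0.167) = 13%.
- For an operation type making up 30% of cases (assumed): P(imbalance above 10 points) = P(|Z| > 0.10 / (√(0.3 × 0.7) × 0.167)) = 19%.
- If delirium is 20 points more common in that type (assumed), a 10-point imbalance moves the observed difference by 0.10 × 20 = 2 points. At 22% delirium the SE of the risk difference is √(0.22 × 0.78) × 0.167 = 6.9 points, so the shift is about 0.3 SE.

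**Gain for continuous endpoints.** Adjustment multiplies the SE by √(1 − R²), where R² is the share of outcome variance that the covariates explain. The documents do not give R², so a range is assumed. The equivalent number is 192 / (1 − R²). The last column is power at 0.467 SD, the difference detectable with 80% power unadjusted (2.80 × 0.167).

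| Assumed R² | CI narrower by | Equivalent unadjusted N | Power at 0.467 SD |
|---|---|---|---|
| 0 | 0% | 192 | 80% |
| 0.05 | 2.5% | 202 | 82% |
| 0.10 | 5.1% | 213 | 84% |
| 0.20 | 10.6% | 240 | 88% |

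**Gain for delirium.** Simulated variance ratios of the standardised to the crude risk difference, under assumed moderate covariate effects, were 0.98, 0.89 and 0.94 at delirium rates of 20%, 22% and 30%. Interval widths scale with the square root: 0.990, 0.943 and 0.970, so about 1%, 6% and 3% narrower.

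**How many terms the data can carry.** At 20% delirium, 0.20 × 48 = 9.6 control events and 0.20 × 192 = 38.4 events in all are expected. Arm (1), center (2) and age (1) make 4 terms, or 38.4/4 = 9.6 events per term. Three or four operation groups add 2 or 3 terms, giving 38.4/6 = 6.4 or 38.4/7 = 5.5. For the primary endpoint, 2% of 192 is 3.8 expected failures, too few for any such model.

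**The case against.** The strongest reply is that nothing here is wrong. Chi-square, Fisher, t and Mann–Whitney tests are valid after randomization, and their error rates and intervals already include chance imbalance at 144 v 48. That stands. A reader might infer that the unadjusted results are biased, or that a difference arising from case mix is spurious. The documents do not support that; it is ordinary sampling error, already counted in the interval.

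A reader might also take the Discussion's phrase "large variation in physiological changes in children which leads to large differences in pharmacokinetic processes" as proof that age matters strongly in this trial. In context it explains why enrollment is limited to ages 3 to 6. It makes age a plausible covariate, but does not show wide variation inside that band. Likewise, the article already acts on pain as a confounder by design: regional techniques after surgery, and pain scored alongside delirium. How far pain differs between operations is not stated.

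The gain is assumed rather than shown, and for binary endpoints it is small. That stands too. So does the point that adjustment is not free: operation groups need a case mix that the article does not give, and a log-time model alone would lose differences in minutes.

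Finally, an unseen analysis plan could contain adjusted analyses. That is possible, but section 2.7 does not leave the method open: it names the test for each type of endpoint.

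**Conclusion.** The point holds as a loss of precision. Section 2.7 commits the secondary endpoints to tests that ignore the stratification factor and two pre-treatment variables already in hand. Validity is not affected.

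The benefit is modest: intervals about 2.5% to 11% narrower for continuous endpoints at assumed R² of 0.05 to 0.20, about 1% to 6% narrower for delirium, and no gain if the covariates are not prognostic. R², the share of each operation type and the risk contrasts are all assumptions. The change is worthwhile mainly because it is cheap and can still be prespecified. Adjustment chosen after an imbalance has been seen would be post hoc.

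**What to change.** While the trial is recruiting, add to section 2.7, for the secondary endpoints only:

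- **Covariates.** Center, age (continuous) and a small number of operation categories, based on the planned operation and fixed without sight of outcome data by arm. The last condition should be written out, because only participants and postoperative evaluators are blinded (section 2.3).
- **Time to LoC, awakening, extubation and PACU discharge.** A linear model with arm and these covariates, on log time if skewed. Keep the Hodges–Lehmann difference in minutes alongside it.
- **Delirium, moderate or severe pain, PACU remedial drugs and negative behavior.** A logistic model standardised to a risk difference with 95% CI. Drop the operation terms when events are sparse, by a rule stated in advance.
- **Supportive analysis.** The planned unadjusted tests.
- **Exclusions.** Leave the primary endpoint out of this adjustment. Do not adjust for length of surgery, intraoperative drug totals or measured pain, which arise after randomization.

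Cost: a few lines of text, slightly more analysis work, and grouping the operations in advance. No new data or patients are needed.

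### Randomization is stratified by center, but every comparison named in the analysis section is unstratified and the primary non-inferiority interval is stated without center

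*Protocol article*

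**What the plan says.** Section 2.3 (Randomization and masking) states: "Randomization will be stratified by centers to limit baseline imbalance between treatment groups". Section 2.1 names three participating hospitals.

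Section 2.7 (Statistical methods) lists the comparisons by type of endpoint:
- dichotomous endpoints: chi-square, continuity-corrected chi-square or Fisher's exact test;
- normally distributed endpoints: independent-samples t-test with a CI for the difference in means;
- other continuous endpoints: Mann-Whitney test with a Hodges-Lehmann estimate.

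None of these uses center. The primary decision rule is: "Non-inferiority will be assumed if the lower limit of a two-sided 95% CI of the difference between Group R and Group P" in the primary endpoint lies above the margin. Neither an interval method nor a center term is given for it.

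Section 2.6 (Sample size and statistical power) assumes "a proportion of the successful anesthesia induction and maintenance of 98% in both treatment groups", a one-sided alpha of 0.025, 90% power, a margin of −8 percentage points and "an intervention: control ratio of 3: 1". It arrives at 171 children, raised to 192 (144 in Group R, 48 in Group P).

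**The concern.** A factor used to stratify randomization should normally appear in the analysis. Stratifying removes chance imbalance between arms on center. If center also predicts the outcome, an analysis that ignores it leaves between-center variation in the standard error and gives up the precision that stratification was meant to buy. That is plausible here. Remedial drugs and their choice are left to investigator judgment (section 2.4.3), and awakening, extubation and PACU discharge times depend on local practice.

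For the tests in section 2.7 this is a stated choice that departs from section 2.3, not only silence. For the primary interval the text is silent. With so few failures expected, the formula chosen for that interval can move the pass/fail line by one child.

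**Working it through.** **Inputs (section 2.6).** Success 98% in both arms, margin 8 points, one-sided alpha 0.025, power 90%, ratio 3:1, final arms 144 and 48.

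**1. The plan's own figure.** With the unpooled normal approximation:

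n_P = (1.960 + 1.2816)² × [0.98×0.02/3 + 0.98×0.02] / 0.08² = 10.508 × 0.026133 / 0.0064 = 42.9.

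The total is 4 × 42.9 = 171.6, against 171 stated, so the figure is reproduced (172 as whole arms of 129 and 43). Then 171/0.90 = 190, and the next multiple of 4 is 192 = 144 + 48.

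**2. How few failures are expected.** Control failures: 48 × 0.02 = 0.96. P(no control failure) = 0.98^48 = 0.379. At 43 controls these are 0.86 and 0.419.

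**3. What the interval method changes.** Largest number of Group R failures (of 144) that still meets the rule:

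| Control failures (of 48) | 0 | 1 | 2 | 3 | 4 |
|---|---|---|---|---|---|
| Wald | 6 | 6 | 7 | 9 | 10 |
| Miettinen-Nurminen score | 5 | 6 | 8 | 10 | 12 |

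Example: 138/144 against 48/48. The difference is −6/144 = −4.17 points. Wald: −0.0417 − 1.960 × √(0.0417×0.9583/144) = −0.0417 − 0.0326 = −7.4%, which passes. The score lower limit is −8.8%, which fails.

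Wald and score reach different conclusions in 1.8% of trials at 98%/98%. If Group R success were 95–96% with controls at 98% (an assumption), they would differ in 8–9%.

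**4. One-sided error at 144:48.** Exact enumeration of both binomials, with the Group R rate set 8 points below control:

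| True control success | Wald | Score |
|---|---|---|
| 90% | 1.49% | 3.05% |
| 95% | 1.38% | 3.17% |
| 97% | 1.46% | 2.82% |
| 98% | 1.71% | 2.49% |
| 99% | 2.54% | 2.16% |
| 99.5% | 3.53% | 2.11% |
| 100% | 5.25% | 2.31% |

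**5. Power at 98%/98%.** Wald 97.9% and score 96.3% at 144:48; score 93.3% at 129:43.

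**6. Effect of center on the primary rule.** Simulation of 400,000 trials per scenario. It assumes three equal centers (48:16 each) averaging 98% control success, with center rates from no spread up to 100/100/94%. Neither center sizes nor center rates are in the document. One-sided error was 1.65–1.72% for the crude Wald limit and 1.87–2.18% for a center-stratified Wald limit. Power was 97.9–98.1% crude and 97.9–98.8% stratified.

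**The case against.** **The silence may be filled elsewhere.** The article condenses a fuller protocol, and a SAP may exist. Interval formula and stratum adjustment are commonly left to those documents. This stands for the interval method: its absence alone is not an error, and the text does not say that the primary interval will be unstratified. It has less force for the tests, because section 2.7 commits to specific methods by endpoint type and all of them omit the randomization factor.

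**No harm to the primary endpoint is shown.** This stands. In the simulation, leaving center out did not inflate the error, and stratifying gained at most 0.7 points of power. With about one control failure over three centers, at least two control strata would typically have none.

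**Stronger readings that a reader might infer.** One is that the rule doubles the one-sided error, since Wald reaches 5.25%. The document does not support this. It never names Wald, and reproducing 171 with a normal approximation does not show how the data will be analyzed. The 5.25% also needs a true control success of exactly 100%. At the plan's 98%, Wald's error is 1.7%, below nominal, and it passes 2.5% only from about 99%. Another is that the score interval is uniformly better. It is not: it is slightly liberal (2.8–3.2%) if control success is 90–97%, where Wald is conservative.

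**Conclusion.** The point holds as a low-to-moderate one about consistency with the design. Randomization uses center, the named tests do not, and the primary interval is stated without it. Analyzing by the randomization strata costs nothing in patients. Its benefit lies mainly in precision for the secondary endpoints, by an amount that depends on between-center differences the document does not give, so I put no figure on it. For the primary endpoint the gain is small.

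Naming the interval in advance is useful because one child can separate two reasonable methods in a situation (no control failures) that has a 38% chance at the assumed 98%. Overall disagreement at 98%/98% is nevertheless only 1.8%. There is no support for a claim of inflated error at the planning assumptions. The error and power figures for the score method are for its unstratified form and rest on independent binomial outcomes at 144:48 or 129:43.

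**What to change.** In section 2.7, or in the SAP if it is still open:

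1. Name the primary interval as the center-stratified Miettinen-Nurminen score interval for the risk difference (Group R minus Group P), with the unstratified score interval as sensitivity analysis. A score method suits this design because it does not give a stratum zero variance merely because no failure was observed there.
2. Carry center into the secondary comparisons: Cochran-Mantel-Haenszel for binary endpoints, and van Elteren or a linear model with center for continuous ones.
3. If the full protocol or SAP already specifies this, align the wording of section 2.7 with it.

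The cost is two or three sentences and possibly a routine outside the named SPSS package. The sample size does not change. Unstratified score power (96.3%, or 93.3% at 129:43) is 1.6 points below Wald at 144:48 (97.9 − 96.3) but above the planned 90%. A short simulation of the stratified interval with the actual center sizes, run before unblinded data are seen, would confirm its error and power. It should include control success below 98%, where the unstratified score interval is slightly liberal.

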## 3 Discussion

Pediatric anesthesia has consistently been seen as a conundrum for anesthesiologists in various fields of surgery and diagnostic procedures due to a far more stressful response to surgery or invasive operation in the pediatric population than in adults. As a result, it has been well acknowledged that general anesthesia is the preferred anesthetic management option for the pediatric population, with increasing utilization of agents such as propofol, midazolam and dexmedetomidine (Lauder, 2015), and TIVA seems to be more applicable than inhalational anesthesia. Remimazolam, a member of benzodiazepines, exerts its clinical effect by means of highly selective allosteric modulation of the GABAA receptor and shares some properties with both its parent compounds, midazolam and remifentanil. During this past decade, it was widely used as an intravenous agent for general anesthesia, procedural sedation and intensive care unit (ICU) sedation in adults. It exhibited distinctive and amazing advantages concerning pharmacological and pharmacokinetic properties over propofol, midazolam and dexmedetomidine. The findings of several phase III studies (Rex et al., 2018; Pastis et al., 2019; Rex et al., 2021) in sedation for endoscopy have documented a higher procedural success rate, more rapid onset of action, faster time to return to wakefulness from sedation in remimazolam group than in midazolam group, without significant differences regarding safety or adverse effects. A phase III study (Chen et al., 2022) comparing a slow initial dose of remimazolam versus dexmedetomidine for 10 min followed by appropriate maintenance dose in conjunction with continuous infusion of remifentanil to maintain MOAA/S scale <3 for 146 outpatients undergoing FB simultaneously reported that remimazolam-remifentanil had a non-inferior efficacy, better time metrics and hemodynamic stability compared to dexmedetomidine-remifentanil. Moreover, several phase II or III studies with propofol-control have been conducted on adult patients receiving endoscopic procedures (Chen et al., 2020; Chen et al., 2021; Zhang et al., 2021), in which remimazolam showed non-inferior procedural success rate, better respiratory management and hemodynamic stability, and lower incidence of injection site pain than propofol. A Japanese phase IIb/III trial (Doi et al., 2020) evaluating the non-inferior efficacy and safety of remimazolam versus propofol for the induction and maintenance of general anesthesia in adult patients undergoing elective surgery reported a similar pharmacodynamic profile to the above endoscopic therapy studies.

Hence, the striking features of remimazolam include faster onset and offset rates, a shorter half-life than midazolam and dexmedetomidine, lower accumulation and risk of cardiovascular and respiratory depression than propofol, and availability of a reversal agent, which should be sufficient to increase the accuracy of the hypothesis—non-inferior efficacy and more limited AEs of this drug in induction and maintenance of general anesthesia in preschool-age children than propofol. Particularly, it should be suitable for short-term operations and day-surgery where the child needs to be discharged from the hospital as early as possible.

In our research, we will include 192 children aged 3–6 years to explore the efficacy and safety of remimazolam in preschool-age children in consideration of the large variation in physiological changes in children which leads to large differences in pharmacokinetic processes, and the difficulty in establishing peripheral venous access preoperatively in children under 3 years of age. We choose propofol as the control drug instead of midazolam or dexmedetomidine, mainly because propofol is the most commonly used intravenous agent for the induction and maintenance of anesthesia, procedural, and critical care sedation in pediatric patients (Chidambaran et al., 2015). Furthermore, midazolam and dexmedetomidine have always been used as premedications for pediatric patients to relieve anxiety and distress, enhance compliance with anesthesia induction, and reduce the incidence of ED (Lang et al., 2020).

We will make continual adjustments to the infusion rate of investigational drugs in the context of the changing intensity of surgical stimuli as primary guidance and the BIS value as secondary guidance to maintain an optimum depth of anesthesia. Drawing on the “pressure, rate, sweating and tears” (PRST) scoring system (Russell, 1993), light anesthesia is defined as the occurrence of at least one of the following signs: patient movement, sweating, tears, hypertension and tachycardia (SBP and HR exceeding 25% (Lei et al., 2017) of the baseline value for more than 5min), or clear and substantial elevations in SBP or HR. Hypotension is SBP <70 mmHg + (2 x age in years) for a further 5 min. This is in accordance with previously described guidelines for hypotension by the Pediatric Advanced Life Support Provider Manual (Haque and Zaritsky, 2007). Bradycardia is usually defined as a heart rate below the lowest normal value for age. Thus, we define bradycardia as HR < 70 bpm for a further 5 min in children aged 3–6 years with reference to normal values for age (Baruteau et al., 2016). As everyone knows, the vagal excitatory reflex and harm may be magnified at the transient and extreme surgical stimuli. Consequently, it is the few minutes of SBP and HR fluctuations that matter. We then define hypertension, tachycardia, hypotension and bradycardia sustained for at least 5 cumulative minutes. It is worth noting that the appearance of clear and substantial elevations in SBP or HR must be immediately adjusted and processed by using remedial drugs.

The electroencephalogram-based (EEG-based) systems have been used for assessing the appropriate depth of general anesthesia. However, the EEG in younger children is increasingly different from that of adults, and the currently available processed EEG devices (BIS Monitor, the Patient State Index (PSI) of the SEDLine brain function monitor or the Narcotrend index) are based on adult EEG data and may not directly apply to the pediatric population accompanying age-related differences (Grasso et al., 2021). Some studies have shown that the BIS value during anesthesia with remimazolam was reported to be higher than with propofol (Doi et al., 2020), even in some cases mean intraoperative BIS values were reported to be over 60 in five out of thirty patients who underwent breast surgery under general anesthesia with remimazolam, and mean intraoperative PSI values were >50 in eight patients out of the thirty patients (Shirozu et al., 2022). Likewise, it was reported that the single doses of 0.075–0.3 mg/kg in healthy adults resulted in deep sedation (MOAA/S score ≤1) and mean BIS values of 60–70 after dosing (Antonik et al., 2012). Our pre-test data in pediatric patients under general anesthesia with remimazolam showed a similar experimental result—satisfactory hypnotic efficacy but mean BIS values of over 60 throughout the period of anesthesia induction and maintenance. Although PSI showed a definite dose-response relationship under remimazolam bolus injection, PSI does not appear to be a reliable surrogate of LoC (Chae et al., 2022). The correlation between the Narcotrend Index and MOAA/S score was relatively weak and inconsistent, suggesting that the Narcotrend Index might be less suitable for monitoring the sedative effect if remimazolam is administered alone (Eisenried et al., 2020). Accordingly, the BIS will be monitored continuously during surgery as secondary guidance instead of primary guidance to maintain an optimum depth of anesthesia in the protocol. It can indeed be seen that lack of reliable depth of anesthesia monitoring might keep pediatric patients under the potential risk of deep anesthesia or intraoperative awareness during the procedure. This may increase the incidence of a negative impact on short and long-term outcomes. A semistructured Brice questionnaire could be used in children aged older than 5 years to evaluate the incidence of suspected and true awareness, but regrettably, does not apply to the children within this protocol aged less than 5 years because of their inability to accurately answer the questions asked in the questionnaire (Lee et al., 2021). Therefore, the main purpose of PAED scale and PHBQ-AS on day 3 postoperatively is to remedy this imperfection to some extent. Pain is a key confounding factor in the diagnosis of ED and the evaluation of negative behavior change postoperatively, and so regional anesthetic techniques (local infiltration anesthesia, nerve block or sacral anesthesia) could be admitted to offer control of postoperative pain after the end of surgery in this protocol. Both FLACC scale and PAED scale will be assessed at the same time to avoid conflating symptoms and actions secondary to postoperative pain with signs and symptoms of ED mainly owing to the remarkable similarities between the two clinical symptoms. We will perform the PHBQ-AS on day 3 postoperatively to quantify the apparent alleviation in pain and anxiety for most children discharged from a hospital.

There are several similarities in terms of pharmacological and pharmacokinetic characterization between remimazolam and midazolam commonly given as intraoperative or preoperative agents for anxiety control as well as preventive therapy for ED in children (Urits et al., 2020). Other interesting findings have shown remimazolam besylate, compared with dexmedetomidine, was equally effective in relieving agitation in older patients aged ≥70 years following orthopedic surgery (Deng et al., 2022) and remimazolam provided a non-inferiority quality of recovery (QoR) on postoperative day 1 to propofol for general anesthesia in female patients aged 20–65 years undergoing thyroid surgery (Choi et al., 2022). The assessment of QoR on day 1 postoperatively depends on the QoR-15 questionnaire, which is a global measure of recovery after surgery. These outcomes should contribute to the holding of another hypothesis—remimazolam applied on induction and maintenance of general anesthesia could be identically effective in decreasing the incidence of ED and negative behaviors after hospitalization in preschool-age children to propofol.
